### Data management {19}

For each assessment (tests 1 to 6), data are collected in raw scores (number or percentage of errors and completion time in seconds), percentiles or standard deviations. These data are reported on the CRF by each associate investigator, and are checked and centralized on an Excel spreadsheet by the coordinating investigator. In accordance with the Good Clinical Practices of Decree No. 64 of November 30, 2006 (JORF No. 277), at the end of the trial, all documents relating to the protocol are archived for a minimum of 15 years by the principal investigator in a locked room with sufficient guarantees of protection against fire, water damage, light or any malicious acts. Given that all interventions use at least two computerized training programs, treatment fidelity and performance during training will be assessed by analyzing the log files and user data.

### Confidentiality {27}

For the duration of the study, information and data will be collected and archived anonymously by a numeric code randomly assigned to each participant.

Experimental data, collected directly on computer, will be transferred (and deleted from the computer used for the study) to a network secured by an identifier and a password, whose access is limited to the study authors. Experimental data collected in paper format will be entered directly into the observation workbook and will be considered as source data.

### Plans for collection, laboratory evaluation and storage of biological specimens for genetic or molecular analysis in this trial/future use {33}

Not applicable, no samples collected.

## Statistical methods

### Statistical methods for primary and secondary outcomes {20a}

The statistical analysis will first include a descriptive analysis of the study population and the parameters studied, globally and by training group, with an assessment of absolute and relative frequencies (and their 95% confidence intervals) for categorical variables, and an assessment of means and standard deviations, medians and interquartiles for quantitative variables. A flowchart will present the number of eligible participants, the number of participants randomized into each group and the number of participants included in the final analysis. The characteristics of participants lost to follow-up during the study will be described. As recommended in the Consort recommendations, participant characteristics will be compared between the two groups at inclusion from a clinical and statistical perspective. Before each analysis is carried out, the conditions of application of the tests used will be verified. The different tests will be considered significant at the 5% threshold (first species risk).

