## Trial design {8}

The trial is a two-arm crossover multicenter randomized controlled trial conducted in France with 76 speech-language therapists as associate investigators. Randomization will be ensured by means of block randomization with a 1/1 allocation. The framework of this trial corresponds to its overall objective which is to test the superiority of a multimodal and intensive training compared with a non-specific and non-intensive training. Indeed, all children who come to seek dyslexia therapy with a speech and language therapist deserve to be helped and it is ethically difficult to justify that we postpone a potentially effective intervention for 16 months (i.e., children would lose more than an entire year, which is a lot during such a critical developmental phase). For these ethical reasons, we have decided to not to include a no-training control group.

The experiment will take place in three phases over 16 months (see Fig. 2):Phase 1 (baseline): All dyslexic readers participate in one 30-minute session per week with the speech-language therapist for 8 weeks without intensive home training. Reading and spelling exercises are performed as part of the speech and language therapy.Phase 2 (intervention): All dyslexics receive three types of intensive interventions, phonological (PHO), visual-attentional (VA), and cross-modal (CM), that last 2 month each. The order of the first two interventions (PHO and VA) is swapped in two randomly assigned groups of 60 dyslexics each. All children also participate in one 30-minute session per week with the speech-language therapist. For 15 minutes, the speech-language therapist checks that the at-home training instructions are clearly understood. The rest of the session is focused on reading and spelling exercises.

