### Eligibility criteria {10}

#### Criteria for inclusion

Age ≥ 8 years old and ≤ 13 years old.Diagnosis of a specific neurodevelopmental reading disorder, according to DSM-5 criteria, with scores ≤ − 1.5 standard deviation from the mean on leximetric tests: Alouette [113, 114], Evaléo 6–15© [115] or Evalec© [116].Phonological deficit: Scores in speed or accuracy lower than 1.5 SD from the mean for phonemic analysis tasks or non-word repetition tasks or automatized quick naming tasks of the Evalec Battery.Visual-attentional deficit: Scores in speed or accuracy lower than 1.5 SD from the average for global or partial reporting tasks of the Evadys© test [117] or for attentional focus tasks of the Sigl© test [118].All children have both at least one phonological deficit and at least one visual-attentional deficit.Family home equipped with a connected computer set up for daily training sessions.Informed consent signed by both parents or by a representative of parental authority.

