## Assignment of interventions: allocation and blinding

### Allocation

### Sequence generation {16a}

Randomization is performed centrally at the Delegation for Clinical Research and Innovation of Nice (DRCI) of the Nice University Hospital Center by e-mail. Randomization is not stratified on the participating centers; the recruitment is competitive.

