### Statistical analysis

To assess the gains for each dependent variable (reading, spelling and reading comprehension scores) in each group (1 and 2) and for the total sample, we will calculate the means difference and confidence intervals between T1 and T2 (Phase 1 without training), between T2 and T4 (Phase 2 after 16 weeks of training), between T4 and T5 (Phase 2 after 24 weeks of training), and between T5 and T6 (Phase 3 after 8 weeks without training).The gains between T1 and T2 will be compared with the gains between T2 and T4, between T4 and T5, and between T5 and T6 to determine whether the T2T4, T4T5, and T5T6 differences represent a significantly greater gain compared to the no training phase (T1T2).

To measure the effect of each type of training, we will calculate the effect size, *Cohen’s d* or *η*^*2*^, from the gains of each dependent variable. Cohen’s d scores of 0.3, 0.5 and 0.8 are considered to represent small, medium and large effect sizes, respectively.3.To determine whether the order of PHO/VA versus VA/PHO training leads to different effects, we will perform a repeated Anova with cross-over between groups to compare the gains between T2 and T4 of each group, controlling for gains between T2 and T1 without training. This analysis will also allow us to determine if there is a significant difference between the effects of 8 weeks of phonological training and 8 weeks of visual-attentional training between T2 and T3.4.Exploratory factor analysis will verify that all the items in the questionnaires (pre-test and post-test Likert scale) or, failing that, some of them can be combined into a score. If necessary, the composite scores will be analyzed as continuous variables. If not, graphical representations in the form of histograms will be used to visualize the variations, and χ^**2**^ tests will be carried out.

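### Inclusion characteristics are to be compared statistically between the randomised groups, which does not show whether an imbalance matters, while the order and PHO-versus-VA analyses do not adjust for age

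*Protocol article*

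**What the plan says.** In the Protocol article, Statistical methods for primary and secondary outcomes {20a} first plans a descriptive analysis, overall and by training group. It then adds that "participant characteristics will be compared between the two groups at inclusion from a clinical and statistical perspective". Two sentences later it states that "The different tests will be considered significant at the 5% threshold", with no exception for the comparison at inclusion. It does not say what will be done with the result.

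On allocation, Trial design {8} says "Randomization will be ensured by means of block randomization with a 1/1 allocation", and Sequence generation {16a} says "Randomization is not stratified on the participating centers; the recruitment is competitive". Neither section names any stratification factor. The inclusion criterion for age is "Age ≥ 8 years old and ≤ 13 years old".

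The Statistical analysis section defines the order comparison as a repeated ANOVA with cross-over that will "compare the gains between T2 and T4 of each group, controlling for gains between T2 and T1 without training". The same analysis is to serve for PHO against VA between T2 and T3. The T1-T2 gain is the only control variable named. Data management {19} says that "data are collected in raw scores (number or percentage of errors and completion time in seconds), percentiles or standard deviations", and no section states which of these scales enters the analysis.

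**The concern.** If central allocation is carried out properly, any difference between the groups at inclusion has arisen by chance. A test at inclusion then examines a hypothesis already known to be true. A significant result does not show that the imbalance affects the outcome, and a non-significant one does not show that it is harmless. What matters is how strongly the characteristic predicts the outcome, and the test carries no information on that.

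Age is a plausible predictor in a sample spanning five or six years of reading development, and it is already collected. It has no place in the model for the only comparison that randomisation supports. That comparison also bears on Hypothesis 5, which expects no significant difference between PHO and VA at test 3. A chance age imbalance could add to such a difference or mask one. At stake are some precision and some conditional bias in a secondary contrast.

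**Working it through.** The plan gives no figure on this point, so there is none to reproduce. The sample size is not in question.

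**1. Tests at inclusion.** Each test at 5% has a 0.05 chance of significance when the null hypothesis is true. The plan does not count the characteristics. Table 2 has 17 measure rows; two of them (oral language and matrix reasoning) are given only to children without an earlier assessment. Taking one score per row as an illustration:
- expected number significant by chance: 17 × 0.05 = 0.85, whatever the correlation between scores;
- chance of at least one, if independent: 1 − 0.95^17 = 0.58.

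The second figure is an upper one, because the reading measures overlap and are correlated.

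**2. Age imbalance that the test lets through.** With 60 per group, the standard error of a mean difference is √(2/60) = 0.183 SD. A difference up to 1.96 × 0.183 = 0.36 SD is non-significant. The age distribution is not given. Assume it uniform over 5 years (up to the 13th birthday) or 6 years (through age 13):
- SD = 5/√12 = 1.44 years, or 6/√12 = 1.73 years;
- largest non-significant difference = 0.52 years, or 0.62 years.

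**3. Effect of that imbalance on the contrast.** Let r be the partial correlation of age with the gain after the T1-T2 control. The documents do not give it; r = 0.2 to 0.3 is assumed. The shift at the edge of significance is r × 0.36 SD of the gain that remains after that control:
- r = 0.2: 0.07 SD;
- r = 0.3: 0.11 SD.

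**4. Type I error without age in the model.** This comes from a simulation of two standard normal group differences (age and outcome) correlated at r, with 400,000 draws.

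| | r = 0.2 | r = 0.3 |
|---|---|---|
| Over all randomisations | 5% | 5% |
| Age difference significant at 5% | 7% | 9% |
| Age difference between the 20% and 5% points | 5.7% | 6.4% |

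The error rate rises in the last row too, although the test at inclusion would report nothing there.

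**5. Gain from adjusting.** Residual variance is multiplied by 1 − r²:
- r = 0.2: 0.96, a cut of 4%; standard error × √0.96 = 0.98;
- r = 0.3: 0.91, a cut of 9%; standard error × √0.91 = 0.95.

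**The case against.** The strongest reply is that nothing depends on the comparison at inclusion. It selects no covariate and changes no model, and it is paired with a clinical view. A reader might infer that covariates will be picked from whatever turns out significant. The article does not say so, and its one control variable is fixed in advance. This stands: dropping the p-values changes no trial result by itself. The 5% threshold is also stated for tests in general, so applying it to inclusion is the natural reading and not an explicit statement.

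Second, age is already partly handled. Gains remove stable differences in level, the T1-T2 gain captures some of each child's rate of progress, and age-normed scores would remove more. This stands as a reason for modest size. It does not settle the matter, because a gain over two months is a noisy stand-in for age and norm-referenced scores are only one of the recorded scales.

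Third, an analysis plan that is not shown might add covariates, and the article rules out stratification only by centre. Both are true. The article does name the control variable for this analysis, however, and age is not it. It describes no stratification by age.

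Fourth, in an open-label trial a difference at inclusion could reveal faulty allocation, so such tests are not strictly limited to chance findings. That is fair, but the plan does not give it as their purpose.

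Two further readings go too far. A reader might quote 64% or 72% as the chance of a false alarm (1 − 0.95^20 and 1 − 0.95^25). Those need 20 or 25 independent characteristics, and the document supports neither the count nor the independence. A reader might also infer that the main result is confounded by age. The main objective compares phases within each child, so an age imbalance between the groups does not confound it.

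**Conclusion.** The point holds as a minor one. The statistical comparison at inclusion is uninformative about whether an imbalance matters, and has no stated use. The order and PHO-versus-VA analyses would be better with age in the model than with the T1-T2 gain alone. Under an assumed partial correlation of 0.2 to 0.3, the benefit is a standard error about 2% to 5% smaller and protection against a chance shift of up to about 0.07 to 0.11 SD that a test at inclusion would not flag. If age predicts little once gains and the T1-T2 control are used, the benefit is close to nil. The unadjusted analysis is valid on average over randomisations, so this is not a claim that the plan's between-group test is invalid.

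**What to change.** In {20a}, replace the statistical comparison at inclusion with a table of characteristics by group (means, SDs, medians, frequencies) without p-values. The descriptive analysis by group already planned there supplies its content.

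In Statistical analysis, state that the between-group analyses (PHO/VA against VA/PHO over T2-T4, and PHO against VA over T2-T3) include age or school grade as a covariate alongside the T1-T2 gain, whatever the table shows. Choose one of the two and fix it before the data are analysed. Name the score scale (raw, percentile or SD) in the same place, since it governs how much age can matter.

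The cost is a sentence or two of wording and one degree of freedom. For a single between-group contrast on 120 children, with intercept, group and T1-T2 gain in the model, residual degrees of freedom fall from 120 − 3 = 117 to 116. No new data are needed and the sample size does not change.

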## Objectives {7}

### Main objective

The main objective of this study is to assess whether the combination of three types of intensive interventions (phase 2) improve reading and spelling skills compared to baseline (i.e., non-intensive intervention, phase 1).

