### Main hypothesis

Intensive and specific multimodal training significantly improves reading (fluency, comprehension) and spelling skills compared to a conventional non-intensive and non-specific therapy. These effects of intervention will be tracked after the three training phases (test 5) and 2 months later (test 6).

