## Interventions

### Explanation for the choice of comparators {6b}

#### Main evaluation criteria

Reading efficiency is measured at inclusion (Test 1), at the end of phase 1 without intensive training (Test 2), at the end of the three training periods of phase 2 (Test 5) and after phase 3, i.e., 2 months after the training has stopped (Test 6) by five reading tests:Alouette©, a widely used standardized French reading test, measures speed and accuracy when reading a meaningless text and provides a reading age [113] and both speed and accuracy scores [114].DeltaText© measures speed and accuracy of meaningless texts matched in number of words, length and complexity [119].Mouette-Pingouin© measures the speed and accuracy of word identification of meaningful texts matched in length and complexity to control for a test/re-test effect using two texts controlled for word number and word frequency [115].Eval2M© measures the speed and accuracy of identification of words presented in columns [115].Evalec© measures the respective speed and accuracy of identification of regular words, irregular words and pseudowords [116].

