#### Secondary evaluation criteria

Related to the secondary objectives:Reading efficiency after the phonology training and after visual-attentional training will be measured by the five reading tests in Test 3 for the two groups (G1: PHO/VA/CM, G2: VA/PHO/CM).Reading efficiency after the two phonological and visual-attentional training periods conducted in a different chronological order in each group, will be measured by the five reading tests in T4 for the two groups.Spelling skills will be measured by Chronosdictées© [120] which proposes two versions with sentences matched in length, lexical frequency and phonetic complexity.Reading comprehension will be measured by the closure test ORLEC L3© [121, 122].Reading disorder impact (reading interest, academic performance and self-esteem) will be measured by two questionnaires completed by each child and his or her parents, in which they express their degree of agreement or disagreement.

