### Sample size {14}

In a pilot study on 20 patients with dyslexia, we determined that the effect size on reading efficiency between classical rehabilitation (baseline) and intensive rehabilitation was Cohen d = 0.867. Given that the literature on interventions for children and adolescents with reading disabilities gives effect sizes of 0.322 for phonological interventions (see [34]), expected effects on reading skills of a multimodal phonological, visual-attentional and cross-modal intervention should be greater. However, we preferred to be conservative and reduced the expected effect size to Cohen’s d = 0.700. Using G*Power 3.1.9.6, we found *n* = 55 per group. With an estimated drop-out rate of 10%, we will therefore include 120 participants.

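### Neither the primary reading score nor the primary contrast is fixed, the stated threshold is 5% for the different tests, and the statements of aim disagree on spelling and comprehension

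*Protocol article*

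**What the plan says.** Under Main evaluation criteria, reading efficiency is measured at Tests 1, 2, 5 and 6, the last of these "2 months after the training has stopped (Test 6) by five reading tests": Alouette, DeltaText, Mouette-Pingouin, Eval2M and Evalec. No test or score leads, and there is no composite or decision rule.

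The error rate is set under Statistical methods {20a}: "The different tests will be considered significant at the 5% threshold (first species risk".

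Under Statistical analysis, mean differences and confidence intervals are calculated for each reading, spelling and comprehension score "in each group (1 and 2) and for the total sample". The gains over T2-T4, T4-T5 and T5-T6 are then each compared with the T1-T2 gain, to see whether they "represent a significantly greater gain compared to the no training phase (T1T2").

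The statements of aim differ:
- The abstract's main objective is reading skills only.
- The main objective in the body is to "improve reading and spelling skills compared to baseline (i.e., non-intensive intervention, phase 1").
- The main hypothesis is that training "significantly improves reading (fluency, comprehension) and spelling skills compared to a conventional non-intensive and non-specific therapy", followed at Tests 5 and 6.
- The Secondary evaluation criteria include spelling, and also comprehension: "Reading comprehension will be measured by the closure test ORLEC L3".

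**The concern.** A confirmatory trial needs one agreed answer to the question of which result decides whether training worked. Here the score, the contrast and even the domain (reading alone, or reading with spelling and comprehension) can be chosen after the data are seen, and the stated threshold is 5% throughout. The trial is open-label, and its main comparison is a child's later gain against the same child's earlier gain. A pre-fixed endpoint is therefore one of the few safeguards left against claiming the main hypothesis on whichever score moved.

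The sample size section makes the gap visible. It uses a single effect size, d = 0.700, for reading efficiency, so the design already presumes one variable that is never defined.

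**Working it through.** **The plan's own figure.** The inputs are d = 0.700, 1:1 allocation and 5%. The article says "Using G*Power 3.1.9.6, we found" 55 per group, without stating power or sidedness. A two-sample t-test with two-sided 5% and 95% power gives 55 per group (80% gives 34, 90% gives 44), so the figure is reproduced, with 95% power inferred. It is a calculation for one test on one variable.

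**Number of scores.** From Main evaluation criteria and Word identification assessment:
- Alouette: speed and accuracy, 2
- DeltaText: errors and time, 2
- Mouette-Pingouin: time and accuracy, 2
- Eval2M: percentage of words read correctly in two minutes, 1
- Evalec: speed and accuracy for three item types, 6

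The sum is 2 + 2 + 2 + 1 + 6 = 13. It becomes 14 if Eval2M gives both speed and accuracy, as the criteria section says, and 15 with the Alouette reading age. If each test is reduced to one efficiency score, it is 5.

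**Bound under independence.** The chance of at least one false rejection is 1 − 0.95^k. For k = 5 this is 22.6%, for k = 13 it is 48.7%, and for k = 13 × 3 = 39 it is 86.5%. The tests are correlated, so these are too high.

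**Allowing for correlation.** This was simulated under no effect and no trend, with scores equally correlated at ρ and the T1-T2 gain shared by all contrasts. The documents give no correlations, so ρ is an assumption. For 13 scores in the total sample, two-sided:

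| ρ between scores | 0.3 | 0.5 | 0.7 | 0.9 |
|---|---|---|---|---|
| One contrast | 42% | 34% | 24% | 14% |
| All three contrasts | 76% | 66% | 51% | 32% |

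A version with repeated measurements correlated 0.85 over time gives nearly the same values (77%, 65% and 52% for three contrasts at ρ = 0.3, 0.5 and 0.7). With 5 scores on one contrast the range is about 15 to 22% for ρ from 0.7 to 0.3. Counting only rejections that favour training, 13 scores on one contrast give about 13 to 21%, where a single test would give 2.5%.

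**Contrast.** The criterion is measured at T1, T2, T5 and T6. The three planned contrasts cover T2-T4, T4-T5 and T5-T6. None is T2 to T5, and the reading tests at T4 are listed as a secondary criterion.

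**Why a repaired contrast must be scaled for time.** T2-T5 lasts 24 weeks and T1-T2 lasts 8. Suppose there is no training effect but steady growth of g SD per 8 weeks, a correlation over time of 0.85, and 120 × 0.9 = 108 children (g and the correlation are assumptions). The unscaled contrast (T5 − T2) − (T2 − T1) = T5 − 2·T2 + T1 has mean 3g − g = 2g, variance 0.15 × (1 + 4 + 1) = 0.90 and standard error √(0.90/108) = 0.091. For g = 0.05 the mean is 0.10, or 1.1 standard errors, and the test rejects 19% of the time. For g = 0.10 it rejects 58% of the time. The scaled contrast (T5 − T2)/3 − (T2 − T1) has mean g − g = 0.

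**The case against.** The choice of score, the hierarchy and the adjustment are often left to an analysis plan, which is not shown here, and a 5% level does not by itself rule out adjustment. This has force against the threshold sentence taken alone. It does not meet the rest: the article gives spelling and comprehension statuses that cannot all be right, and it describes contrasts that omit the period its own main criterion covers. An analysis plan could not agree with all of these statements.

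Some stronger readings are tempting but not supported:
- A reader might multiply 13 scores by three contrasts and three populations to get 117 tests. The words about each group and the total sample govern the mean differences and confidence intervals. The sentence that compares gains names no population, so testing within each group is an inference. If it is done, the error rate rises further.
- A reader might treat all three contrasts as primary. T4-T5 isolates the cross-modal block and T5-T6 bears mainly on stability, and both are largely secondary questions. One contrast in the total sample is the fairer base.
- A reader might conclude that a spurious success on the primary question is likely. On one contrast, and counting benefit only, it is about 13 to 21% with 13 scores and lower with five: well above nominal, but not likely.
- A reader might say that the objectives disagree on comprehension. Neither statement of the main objective mentions it. That conflict is between the main hypothesis and the secondary criteria. On spelling, the two statements of the main objective do differ.

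**Conclusion.** The point stands. The article sets a 5% threshold for the different tests, leaves the primary score and the primary contrast open, and contradicts itself on whether spelling and comprehension belong to the main question. On one contrast in the total sample, the two-sided chance of at least one false rejection is about 24 to 42% with 13 scores and 15 to 22% with five. Testing all three contrasts with 13 scores raises it to about 51 to 77%.

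The sizes rest on assumed correlations of 0.7 to 0.3 between scores, on no trend over time, and on the count of scores. At a correlation of 0.9 with 13 scores, the one-contrast figure is still 14%. The contradictions between sections need no assumption.

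**What to change.** Name one primary variable, for example a mean z-score across the five tests:
- Standardise each score on the T1 mean and SD, and reverse the sign of time and error scores.
- Average speed and accuracy within each test.
- Average Evalec's six scores to one value first, so that each test has equal weight.

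Test it once at 5% in the total sample, on one contrast: (T5 − T2)/3 minus (T2 − T1), the gain per 8 weeks in phase 2 less the phase 1 gain. Treat individual reading scores (with Holm's adjustment), the other contrasts, analyses by group, spelling and comprehension as secondary. Align the abstract, Main objective and Main hypothesis with the Main and Secondary evaluation criteria.

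This needs wording only, with no new data or visits, and should be settled before outcomes are analysed. One test on one variable also matches the form of the sample size calculation. The cost is that fewer single-score results can be called significant. The scaling removes steady growth only; it does not correct for growth that changes pace.
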